### Intervention

#### Content

The BA intervention is informed by the simple BA protocol [38, 40] originally developed for PWP delivery of low-intensity treatment within the IAPT programme [68].

#### Materials

Two workbooks have been developed, one designed for the person with dementia [69] and the other for the informal carer to aid supporting the person with dementia work through the intervention [70]. The workbook for the person with dementia was written in line with national guidance for the development of dementia-friendly written information [71] describing steps of the BA intervention and providing accompanying worksheets. The informal carer workbook provides guidance on how to support the person with dementia implement the steps involved within the BA protocol, alongside additional support to manage in the caring role, informed by an existing self-help intervention for carers of stroke survivors [72]. To maximise acceptability, the content and design of both workbooks were further informed by a series of qualitative studies with people with dementia and their informal carers.

#### Support

A PWP will guide the use of the BA self-help programme, providing a maximum of 12 sessions over 3 months (see Table 1 for the treatment support protocol). These 12 sessions will include one initial assessment session, one setting up support session, up to nine brief telephone support ‘check-ins’ representing minimal contact support [26, 73] to the informal carer and finally, one relapse prevention session. PWPs will follow a structured support protocol, adapted from existing support protocols for PWP assessment and support sessions [68] and brief telephone support sessions [75].

**Table 1 Tab1:** Treatment support protocol

Session number	Attendees	Method of support	Session content	Session duration (min)
1	Person with dementia; informal carer; PWP	Face-to-face	Problem focused assessment to identify the main difficulties with mood and wellbeing experienced by the person with dementia and to introduce the BA approach. The informal carer will also be present to act as an informant if required.	50
2	Person with dementia; informal carer; PWP	Face-to-face	A setting up support session to help establish the protocol for supporting the BA self-help intervention. The rationale for the BA intervention is discussed alongside the procedure for the carer to provide on-going support to the person with dementia.	40
3–11 (maximum)	Informal carer; PWP	Telephone	Minimal contact telephone ‘check-ins’ to check progress made with the intervention, problem solve any difficulties experienced with using the workbook, agree next steps and provide on-going encouragement in the use of the BA self-help workbooks.	Up to 15
12	Person with dementia; informal carer; PWP	Face-to-face	Relapse prevention and provision of information to enhance on-going signposting to appropriate health and social care organisations as needed.	40

#### Setting

All participants will be treated within the ‘BeMe’ primary care mental health service commissioned under the IAPT programme [29] and part of Cornwall Partnership NHS Foundation Trust. All face-to-face sessions will be offered in BeMe offices, community settings or the participants’ home if necessary to ensure inclusion into the study for all those wishing to participate.

#### PWP adherence

With participant consent, all assessment and support sessions will be recorded. To assess adherence to the support protocol, the marking criteria used as the basis of competency assessments within the IAPT training programme for PWPs will be adopted [68]. Necessary adaptations to the support protocol and associated marking criteria have been undertaken to ensure the low-intensity CBT clinical method is consistent and appropriate for use in the study with people with dementia and informal carers. A sample of 20 % of sessions will be randomly selected for each PWP, and adherence to the support protocol will be judged by a clinician otherwise not associated with the study. This clinician will be considered competent to mark the tapes by virtue of having completed and passed the IAPT programme for the training for PWPs themselves and having undertaken additional training with the research team in the use of the marking criteria and adaptations for a dementia population.

### Feasibility outcome measurements (primary outcome measurements)

Data related to study feasibility will be collected to examine the primary study objectives relating to methodological, procedural and clinical uncertainties [47, 48]. Following guidance concerning feasibility study objectives [47], Table 2 provides a summary of feasibility outcomes to be examined, alongside progression criteria (where applicable) to be met in order to progress to develop an application for phase II pilot RCT funding [45].

**Table 2 Tab2:** Feasibility data and method of measurement

Feasibility outcome	Measurement	Progression criteria to phase II pilot RCT
Recruitment	Quantitative data	
	Percentage of people with dementia invited into the study/number of people with dementia in total identified by health professionals	No criteria set
	Number of health professionals required to assist with recruitment into the study	No criteria set
	The time taken (up to 6 months) to recruit up to 50 dyads	No criteria set
	Number of dyads enrolled into the study per week	2 dyads per week
	Percentage of dyads willing to undergo screening/number invited (calculated for GP, PCPD and memory service recruitment)	≥15 %
	Percentage of dyads overall meeting the inclusion criteria/number invited	≥5 %
	Percentage of dyads overall enrolled in the study/number invited	≥5 %
	Qualitative data	
	Reasons for exclusion reported to the research team during health professional screening (GP, PCPDs, memory service)	No criteria set
	Reasons for ineligibility	No criteria set
	Identified barriers to recruitment (reasons for refusal of participation)	No criteria set
Attrition	Quantitative data	
	Percentage of dyads completing post-treatment (3 month) outcome measures	≥70 %
	Reasons for dropout	No criteria set
	Qualitative data	
	Acceptability interviews with non-attendees and poor attendees (informal carers and people with dementia)	No criteria set
Data collection procedures	Quantitative data	
	Time taken and number of sessions to administer the screening measures	≤2 h; ≤2 sessions
	Time taken and number of sessions to administer the baseline assessment	≤2 h; ≤2 sessions
	Time taken and number of sessions to administer the follow-up assessments	≤2 h; ≤2 sessions
	Percentage of missing items per questionnaire	≤10 %
	Qualitative data	
	Acceptability interviews with participants concerning acceptability of research procedures	No criteria set
	Acceptability interviews with PWPs concerning acceptability and feasibility of research procedures	No criteria set
Clinician adherence	Adherence to support protocol as determined by therapy tapes	≥70 %
Clinical delivery	Quantitative data	
	Time between being allocated to PWP and PWP undertaking the assessment session.	≤2 weeks
	Session lengths	No criteria set
	Number of sessions received per dyad	No criteria set
	Settings of sessions (e.g., BeMe, community, home)	No criteria set
	Number of missed appointments	No criteria set
	Number of missed outcome measurement items	No criteria set
	PWP attrition	No criteria set
	Impact of severity of dementia (MMSE score) informing who can engage in the intervention	No criteria set
	Qualitative data	
	Acceptability interviews with participants	No criteria set
	Acceptability interviews with PWPs	No criteria set

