### Setting

Four different settings—general practitioners (GPs), specialist dementia healthcare settings employing Primary Care Dementia Practitioners (PCDP), memory clinics and community outreach in the county of Cornwall (southwest England)—will be utilised to examine feasibility outcomes associated with recruitment. All treatment will be provided by PWPs within ‘step 2’ of an IAPT primary care mental health service adopting a stepped care model [30]. Recruitment setting locations have been selected on the basis of locality of study PWPs from the IAPT service to help increase the feasibility of intervention delivery. Further, recruitment setting types were selected on the basis of recruitment strategies utilised in other depression [50–52] and dementia studies [53, 54].

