#### GP records

GP search and mail-out will be adopted as used successfully in a number of depression trials [50–52]. GP electronic case records will be searched for people with a formal diagnosis of dementia, and a manual screen will be performed to check against the inclusion criteria. Reasons for exclusion will be anonymised and provided to the research team [60]. Participant invitation packages (study invitation letter, study summary sheet, reply slip and reasons for refusal of participation questionnaire) will be sent to people with dementia included in the screen. This package will also include a separate study invitation package to be passed onto an informal carer. People with dementia, or informal carers, will be able to contact the research team by returning the reply slip, telephoning or emailing the research team. Given that telephone reminders by clinicians have been reported to increase recruitment rates [61], non-responders will be provided with telephone follow-up calls by general practice staff. Where phone calls receive no answer, a maximum of four attempts to establish contact will be made over this time period. GPs can also directly refer suitable people with dementia. Study posters and brochures will also be displayed in practice receptions to further advertise the study.

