#### Community outreach

A number of community-based organisations including Memory Cafés, Memory Matters South West, the Alzheimer’s Society, Carers Forum, Disability Cornwall, Dementia Action Alliance, Age UK, Cornwall Carers and Penwith Community Development Trust will be approached to support the study by distributing flyers and invitation packages and displaying posters. In addition, the study will be advertised by distributing study posters and leaflets in other community locations including community day care centres; libraries, banks, bus stops, post offices, supermarkets, cafes and community centres.

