### Statistical analysis

#### Quantitative

Recruitment data: where possible, data will be collected separately from each recruitment setting to determine recruitment rate and methodological uncertainties associated with each specific setting. Data will be collected relating to the type and number of referring sites; number of participants identified at each site; number of invites sent (where possible, this will not be possible with community recruitment), number of potential participants requesting more information, number of consents obtained, number of screens completed, number of baselines completed and number of participants allocated to a PWP. Number of exclusions at each stage and reasons for exclusions will also be reported. The percentage of eligible participants that are recruited will be calculated with exact 95 % confidence intervals using the cii command in Stata software version 14.0.

Feasibility of data collection procedures and acceptability to patients: study protocol deviations along with reasons will be reported to assess both the feasibility and acceptability of the data collection process. The time taken to administer the screening measures, time taken to administer the baseline assessment, time taken to administer the follow-up assessments and the percentage of missing data per outcome measurement collected will also be reported to examine the feasibility and acceptability of data collection procedures.

Attrition (study dropout): the number of participants dropping out of the study will be reported, along with the stage of dropout and reasons where possible. Attrition proportions will be reported with 95 % confidence intervals.

Primary and secondary outcome measurements: descriptive statistics including the means and standard deviations or medians and interquartile ranges will be reported for each outcome measurement at baseline and 3 months post-treatment allocation as these will help to inform the sample size for the pilot RCT and later definitive trial.

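### Two ≥5 % progression criteria divide all dyads by number invited, although invitations cannot be counted for community outreach, so any community dyad raises the percentage

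*Protocol article*

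**What the plan says.** Table 2 of the protocol article lists the feasibility outcomes and, where one is set, the criterion for going on to a pilot RCT application. Four recruitment rows carry a criterion. One is 2 dyads enrolled per week. The other three are percentages of the number invited:

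- ≥15 %: "Percentage of dyads willing to undergo screening/number invited (calculated for GP, PCPD and memory service recruitment"
- ≥5 %: "Percentage of dyads overall meeting the inclusion criteria/number invited"
- ≥5 %: "Percentage of dyads overall enrolled in the study/number invited"

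Only the first of these three names the settings it covers.

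The Setting section names four recruitment settings: GPs, PCDPs, "memory clinics and community outreach in the county of Cornwall (southwest England". Under Community outreach, local organisations "will be approached to support the study by distributing flyers and invitation packages and displaying posters". The quantitative part of the statistical analysis section lists the recruitment data to be collected, including "number of invites sent (where possible, this will not be possible with community recruitment". The GP records section adds a smaller route outside the mail-out: "Study posters and brochures will also be displayed in practice receptions to further advertise the study".

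**The concern.** A yield per invitation is interpretable only if the dyads counted on top come from the people counted underneath. The two ≥5 % rows are calculated overall, and community outreach is one of the settings from which dyads are enrolled. The protocol itself says that setting has no invitation count. A community dyad therefore enters the numerator with nothing to match it in the denominator, and the error can run only upwards.

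These are two of the four quantitative recruitment rows with a criterion, and they help decide whether a pilot RCT application is developed. A yield below 5 % among people actually invited could be recorded as a pass, and the pilot could then be planned on too few invitations. The mismatch also works against the study's aim of comparing recruitment approaches.

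**Working it through.** **Inputs.**
- Threshold: 5 % (Table 2, both rows).
- Maximum enrolment: 50 dyads (Sample size section).
- Community invitations: not countable (Statistical analysis, Quantitative).
- Community share of enrolled dyads, s, and number of counted invitations, N: not given in the protocol. I take s from 0 to 50 % and N from 500 to 1200 as assumptions.

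**The plan's own figures.** The 5 % thresholds are set values with no derivation to reproduce. The one derived figure in the article is the 14 % margin for 80 % follow-up in 50 dyads. The exact 95 % interval for 40/50 is 66.3 % to 90.0 %, and 80 − 66.3 = 13.7 points, so it reproduces. It does not bear on this point.

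**Step 1: size of the inflation.** Let E be the dyads enrolled, c those from the community, and s = c/E.
- Row as written: E/N.
- Same settings above and below: (E − c)/N.
- Ratio of the two: E/(E − c) = 1/(1 − s).

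**Step 2: when the decision changes.** With E = 50, the row as written passes if 50/N ≥ 0.05, that is N ≤ 1000. The restricted row fails if (50 − c)/N < 0.05, that is N > 20 × (50 − c). The two disagree only between these limits.

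| Community dyads c (share s) | Inflation 1/(1−s) | Restricted rate when the row as written is exactly 5.0 % (N = 1000) | Decision differs for N |
|---|---|---|---|
| 0 (0 %) | 1.00 | 5.0 % | never |
| 5 (10 %) | 1.11 | 4.5 % | above 900, up to 1000 |
| 10 (20 %) | 1.25 | 4.0 % | above 800, up to 1000 |
| 15 (30 %) | 1.43 | 3.5 % | above 700, up to 1000 |
| 20 (40 %) | 1.67 | 3.0 % | above 600, up to 1000 |
| 25 (50 %) | 2.00 | 2.5 % | above 500, up to 1000 |

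**Step 3: inside and outside the band, with c = 20.**
- N = 500: 50/500 = 10 % and 30/500 = 6 %. Both pass.
- N = 800: 50/800 = 6.25 % and 30/800 = 3.75 %. The decision changes.
- N = 1200: 50/1200 = 4.2 % and 30/1200 = 2.5 %. Both fail.

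**Step 4: effect on planning.** In the N = 800 case, a pilot that needs 50 dyads from invitations would plan for 50/0.0625 = 800 invitations on the figure as written. The restricted figure implies 50/0.0375, or about 1333. The inflation affects planning even where the decision stays the same.

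The eligibility row follows the same algebra, with eligible dyads in place of enrolled dyads.

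**The case against.** The strongest reply is that *overall* may mean pooled over GP, PCDP and memory service, since a percentage of those invited suggests that the dyads counted are among them. Nothing in the article says this, and the explicit limit on the row directly above points the other way. Even if it was intended, the row needs the same edit, because a progression rule should not be open to two calculations from the same data.

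A second reply is that the analysis section already plans to collect data separately by setting where possible, so a restricted yield could be calculated and a community contribution would be visible. That is true, and it makes the fix cheap. It does not change the criterion as defined.

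Third, these rows do not decide alone. The ≥15 % row is already limited to countable settings, the weekly enrolment criterion needs no invitation count, and a pass leads to an application for a pilot that will itself study recruitment. This limits the consequences and leaves the mismatch in place.

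A reader might also infer that dyads referred directly by a GP or PCDP lack a counted invitation. The documents do not support that. The count is said to be impossible only for community recruitment, nothing says that referred people go uncounted, and PCDPs may hand packages over in person, which can be counted. The GP reception posters and brochures have some basis in the text as an uncounted route, of unknown size.

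**Conclusion.** The point holds on the plain reading of Table 2: the numerator of both ≥5 % criteria covers all settings, while the denominator cannot include one of them. Any community enrolment inflates the percentages by 1/(1−s), and no mechanism in the text pulls them the other way.

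A reader might go further and conclude that the percentages are inflated in fact, or that the criteria will be passed wrongly. The article does not support that. It gives no community share and no invitation count, and there is no inflation if no dyad comes from the community. The decision changes only within a band of invitation numbers: with 50 enrolled and 20 from the community, above 600 and up to 1000. The 800-invitation example is an assumption that lies inside that band. What is established is a badly fixed progression rule with a known direction of error and an unknown size.

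**What to change.** In Table 2, limit both ≥5 % rows to GP, PCDP and memory-service recruitment, in numerator and denominator alike, using the setting limit already on the ≥15 % row. Report eligible and enrolled community dyads separately as counts, outside these percentages. Community dyads should still count towards the 2-dyads-per-week criterion. Dyads who respond only to GP reception posters or brochures should be identified in the recruitment log and reported separately where this is known.

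The cost is a wording change to two table rows and a log entry for how each dyad came in, most of which the planned collection by setting already covers. The downside is that the reported percentages may be less favourable.

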### Clinical outcome measurements (secondary outcome measurements)

To examine the feasibility of the data collection procedures, a number of clinical outcome measures will be collected from people with dementia and their informal carers (see Table 3).

**Table 3 Tab3:** Study clinical outcome measurements by time point

Outcome measure	Time point
Person with dementia	
Sociodemographics	Initial screen
MMSE [56]	Initial screen
GDS-12R [57]	Initial screen, post-treatment follow-up
CSDD [76]	Baseline, post-treatment follow-up
DEMQOL [81]	Baseline, post-treatment follow-up
EQ-5D-3L [82]	Baseline, post-treatment follow-up
Informal carer	
Sociodemographics	Initial screen
PHQ-9 [84]	Initial screen, post-treatment follow-up
GAD-7 [85]	Baseline, post-treatment follow-up
ZBI-12 [86]	Baseline, post-treatment follow-up
CSDD-proxy [76]	Baseline, post-treatment follow-up
SF-12 [87]	Baseline, post-treatment follow-up
EQ-5D-3L [83]	Baseline, post-treatment follow-up
Revised CSRI [88]	Baseline, post-treatment follow-up

*MMSE* mini-mental state examination, *GDS-12R* Geriatric Depression Scale-12 Residential, *CSDD* Cornell Scale for Depression in Dementia, *DEMQOL* Dementia Quality of Life Measure, *EQ-5D-3L* EuroQol-5D-3L, *PHQ-9*, Health Questionnaire-9, *GAD-7* Generalised Anxiety Disorder 7-Item Scale, ZBI-12 Zarit Caregiver Burden Interview Short Form, *SF-12* 12-Item Short Form Health Survey, *CSRI* Client Service Receipt Inventory

#### People with dementia

The Cornell Scale for Depression in Dementia (CSDD) [76] will be used to assess severity of depressive symptoms, alongside the GDS-12R [48]. The CSDD [71] will be used to assess severity of depressive symptoms, alongside the GDS-12R [57, 77]. The CSDD is an interview-based questionnaire conducted with both the person with dementia and an informal carer as a proxy measure and demonstrated to be a reliable and valid measure for people with both mild and moderate-to-severe levels of dementia [78, 79]. The GD-12R is reliable for people with moderate-to-severe levels of dementia [57, 77] and recommended for use in psychosocial intervention research for people with dementia [80]. Quality of life will be examined through the Dementia Quality of Life measure [81] and the EuroQol-5D-3L (EQ-5D-3L) [82] validated in a mild-to-moderate dementia population [83].

#### Informal carers

The PHQ-9 [84] and the Generalised Anxiety Disorder Questionnaire (GAD-7) [85] will be administered to assess severity of depressive and anxious symptoms, respectively. Carer burden will be measured through the administration of the Zarit Caregiver Burden Interview Short Form (ZBI-12) [86]. Quality of life will be assessed through the Medical Outcome Survey Short Form 12 (SF-12) [87] and EQ-5D-3L [82]. Health and social care use, for both the person with dementia and informal carer, will be collected via the administration of an adapted version of the Client Socio-Demographic and Service Receipt Inventory (CSRI) [88], based on two versions developed for carers of stroke survivors [74, 89]. In addition, the CSDD-proxy [76] will be administered to informal carers to collect further information concerning the severity of depressive symptoms in the person with dementia.

#### Sociodemographics and clinical characteristics

During the initial screen, various background, clinical and socio-demographic characteristics—age, gender, ethnic background, relationship status, employment status, highest level of academic qualification, yearly household income, chronic physical health conditions—will be collected from people with dementia and informal carers. This will be supplemented by the additional collection of dementia subtype diagnosed and date of diagnosis from the person with dementia. Informal carers will also be asked to confirm the dementia subtype diagnosed and date of diagnosis as well as yearly household income (if the carer does not live with the person with dementia), length of time caring, if the carer lives with the person with dementia, provision of care before diagnosis of dementia, receipt of support services in the home, hours of support services received in the home per week and hours of caring per week.

